#### Primary outcome measure

The primary outcome and endpoint is a combined measure of depression and anxiety at week 21 (*t*_4_, 2-month follow-up) as indicated by the Patient Health Questionnaire Anxiety and Depression Scale (PHQ-ADS). The PHQ-ADS is a validated measure of the combined sum score of the Patient Health Questionnaire depression module (PHQ-9) [55] and Generalized Anxiety Disorder (GAD-7) [56] questionnaire (see secondary outcomes). Answer options for both the PHQ-9 and GAD-7 are ‘not at all’ (0), ‘several days’ (1), ‘more than half the days’ (2), and ‘nearly every day’ (3) with a sum score of 0–48.

#### Secondary outcome measures

Symptoms of depression and anxiety during the preceding two weeks will be measured by the nine-item PHQ-9 [55] and the seven-item GAD-7 [56] respectively. Answers on both questionnaires are scored on a 0–3 Likert scale (PHQ-9: range 0–27; GAD-7: range 0–21) with higher scores indicating higher symptomatology. For both questionnaires, a cut-off score of 10 will be used [56, 57]. In addition to the nine items, the PHQ-9 asks: “If you checked off any problems, how difficult have these problems made it for you to do your work, take care of things at home, or get along with other people?” which is answered on a four-point Likert scale ranging from ‘not difficult at all’ to ‘extremely difficult’. The Polish version of the PHQ-9 has been validated [58]. The Polish version of the GAD-7 has not been validated yet but has recently been used in various studies to assess anxiety during the COVID-19 pandemic in Poland and shown high internal consistency [59–61].

Symptoms of PTSD during the past month will be measured by the 8-item PCL-5 [62], which is a shortened version of the 20-item PTSD Checklist for DSM-5 (PCL-C) [63]. Items are rated on a 0–4 scale (0–32), with higher scores indicating higher levels of symptoms. The Polish version of the 20-item PCL-5 has been found to have good psychometric properties [64].

Outcome-based resilience will be operationalised as an individual’s deviation from the sample-normalised stressor reactivity (SR) line. To this end, a measure of stressor exposure has been developed based on the Mainz Inventory of Microstressors (MIMIS) [65] and similar measures [66]. The stressor lists were further adapted to fit the target population and shortened to minimize burden of participants. The questionnaire consists of 22 items measuring life events (three items), and general (six items), COVID-related (five items) and migrant specific (eight items) stressors. Life events are measured on a five-point Likert scale (0–4) rating severity and stressors are measured on a four-point Likert scale (0–3) rating how often something occurred. The sample’s normative stressor reactivity will be calculated by regressing stressor exposure (E; as measured by the stressor lists) against mental health symptoms (P; as measured by PHQ-ADS, PHQ-9, GAD-7). For the purpose of building the SR score, the E score that explains the most variance of mental health symptoms will be used. The best fitting regression model will be taken as the sample’s E-P line. Individual SR scores are then calculated as the residuals to the E-P line, where a positive deviation denotes less resilient outcomes and negative scores more resilient outcomes, respectively.

Positive appraisal style, a factor leading to resilience, will be measured with the Positive Appraisal Style Scale, content-focused (PASS-content) [67]. It consists of 12 items focusing on how participants usually act, feel, and think in stressful situations. Scores range from 1 (never) to 4 (almost always; total range 12–48).

Quality of life will be measured by the EuroQol 5-dimensional descriptive system—5-level version (EQ-5D-5L) which consists of the EQ-5D (part 1) and EQ-VAS (part 2) [68]. The EQ-5D consists of five items rating the level of impairment across the dimensions of mobility, self-care, usual activities, pain/discomfort, and anxiety/depression. Each dimension has 5 levels: no problems, slight problems, moderate problems, severe problems and extreme problems. The EQ-VAS consists of a visual, analogue scale with as endpoints ‘the best’ [1] and ‘the worst’ [5] health you can imagine. The EQ-5D-5L has been used widely and is available in over 150 languages, including Polish, also for collection by laptop, tablet or Castor EDC [69].

To examine cost-effectiveness, health service utilization and the effect of ill-health on participants’ and their family/friends’ employment over the past 2 (*t*_2_, *t*_3_, *t*_4_) or 3 (*t*_1_) months will be measured with an adapted version of the Client Service Receipt Inventory (CSRI) [70]. The CSRI has been further adapted to fit the target population of this study. Health service utilization focuses on 12 types of health care providers, as well as in- and out-patient hospital services. If utilization of a health service is indicated, follow-up questions will be asked regarding the contact, e.g. number of visits, type (in-person/online) and duration of contact, location (Netherlands/Poland), travel and waiting time, and travel costs. Additionally, trial costs (e.g. training, supervision, intervention facilitator time) are collected.

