## Analysis

### Sample size

We aim to detect a small-to-medium Cohen’s *d* effect size of 0.3 on the PHQ-ADS composite score (primary outcome) at the *t*_*4*_ follow-up assessment point, which is based on previous RCTs on PM + [28, 29]. Power calculations suggested a minimum sample size of 74 per group (power = 0.95, α = 0.05, two-sided). With an expected 30% attrition at *t*_*4*_, we aim to include 212 study participants (intervention group: *n* = 106, control group: *n* = 106) over an 18-month inclusion period.

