#### Quantitative data (RCT)

Intention-to-treat (ITT) and per-protocol (PP) analysis will be conducted for both the primary and secondary outcomes. ITT analysis will include all randomized participants (*N* = 212). PP analysis will include participants in the intervention group only if they have (a) clicked through at least three (out of five) modules of the DWM web application, and (b), if they qualified for PM + in terms of K10-distress score at *t*_2,_ attended at least four (out of five) PM + sessions. ITT analysis of the primary outcome will be used to answer the main research question.

To compare differences between the two treatment groups at baseline, t-tests (continuous variables) and chi-squared tests (categorical variables) will be conducted for normally distributed data. For continuous non-normally distributed data, Mann–Whitney tests will be conducted.

To estimate the treatment effect on the primary outcome at *t*_2_, *t*_3_, and *t*_4_, with *t*_4_ being our primary time point of interest, a linear mixed model will be used. This model will have time and treatment as fixed effects (as well as their interaction parameters), a baseline measure of the PHQ-ADS as a covariate, and subjects as random effects. The mean difference between the two treatment groups at each assessment with a 95% confidence interval will be obtained from this mixed model. The same linear mixed model will be used to estimate the effect of the DWM/PM + stepped-care programme on secondary outcomes: symptoms of depression (PHQ-9), anxiety (GAD-7), PTSD (PCL-5), quality of life (EQ-5D-5L), and an outcome-based resilience variable, operationalised as the PHQ-ADS total score against stressor exposure [78].

Missing data will not be imputed but will be treated as missing at random (MAR) as linear mixed models can handle missing data. If some items of a particular scale are missing (i.e. < 50%), the Corrected Item Mean Substitution method will be used [79]. This method uses the item mean across participants of the same study group and time point, weighted by the subject’s mean of completed items. All the above-mentioned analyses will be performed using Jamovi version 2.3.26 [80]. Jamovi is an open-source graphical user interface for R.

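### The regression behind the resilience score is worded with outcome and predictor swapped, contradicting the score's own sign rule and the analysis section; one sentence needs correcting.

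*Protocol article*

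**What the plan says.** Outcome-based resilience is a secondary outcome, compared between arms with the same linear mixed model as the primary outcome. Two places in the protocol article define it.

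**Study measures, Secondary outcome measures.** This is the only place that sets out the computation. It has four elements:
- The line is obtained by "regressing stressor exposure (E; as measured by the stressor lists) against mental health symptoms".
- Among candidate exposure scores, "the E score that explains the most variance of mental health symptoms will be used".
- "Individual SR scores are then calculated as the residuals to the E-P line".
- The sign is read so that "a positive deviation denotes less resilient outcomes and negative scores more resilient outcomes".

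**Data analysis, Quantitative data (RCT).** The resilience variable entered in the mixed model is "operationalised as the PHQ-ADS total score against stressor exposure".

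**The concern.** In ordinary usage the variable that is regressed is the dependent one. The first element therefore makes exposure the outcome and symptoms the predictor. A positive residual from that fit means that a person reports more stressors than their symptom level predicts, in other words few symptoms for the load carried. That is the more resilient case, yet the sign rule calls it less resilient. The computing clause and the sign rule cannot both be followed.

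The analysis section names the variables in the reverse order. Both places use the word *against*, so no single reading of that word reconciles them: whichever variable it marks as the outcome in one place, it marks the other in the second.

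At stake is the direction and content of one secondary outcome. An analyst who builds the score from the computing sentence and keeps the stated sign would report an improvement in symptoms as a loss of resilience.

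**Working it through.** The article reports no figure for this score, so there is none to reproduce. The check is on sign and content.

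**Inputs**
- Treatment effect on symptoms: d = 0.3, from the Sample size section, used for illustration.
- Effect on exposure: none (assumption).
- E-P correlation r: not given in the article. Assumed 0.3, 0.5 and 0.6, with 0.2 to 0.7 as a wider range.
- E and P scaled to SD 1 within arm, 1:1 allocation.

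**Intended direction, P on E.** The residual is P - rE, with SD sqrt(1 - r²). Treatment moves P by -0.3 and leaves E alone, so the standardised arm difference is -0.3 / sqrt(1 - r²).

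**Literal direction, E on P.** The residual is E - rP, with the same SD. Treatment moves it by -r × (-0.3) = +0.3r, so the standardised arm difference is +0.3r / sqrt(1 - r²). The residual's correlation with P is 0 by construction, and with E it is sqrt(1 - r²).

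| r | P on E | E on P | corr. of E-on-P residual with E |
|---|---|---|---|
| 0.3 | -0.3/0.954 = -0.31 | +0.09/0.954 = +0.09 | 0.95 |
| 0.5 | -0.3/0.866 = -0.35 | +0.15/0.866 = +0.17 | 0.87 |
| 0.6 | -0.3/0.800 = -0.38 | +0.18/0.800 = +0.23 | 0.80 |

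These formulas ignore the small spread that the arm effect adds to P in the pooled sample. A simulation of 400,000 subjects per setting, which includes it, gives -0.312, -0.341 and -0.371 for P on E, and +0.094, +0.170 and +0.224 for E on P. Over r = 0.2 to 0.7 the simulated ranges are -0.31 to -0.41 and +0.06 to +0.29. The signs hold for any positive r.

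**Reversing the sign would not repair the literal score.** The two residuals correlate at -r, so they are different variables. Under joint normality, the share of people whose two residuals have opposite signs is 1/2 + arcsin(r)/π, which is 60%, 67% and 70% at r = 0.3, 0.5 and 0.6. Flipping the sign of the E-on-P residual would correct its direction but leave it uncorrelated with symptoms.

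**Which direction does the rest of the text support?**
- Sentence on explained variance: E explains and P is explained, so P on E.
- Sign rule: a positive residual means less resilient only if it means more symptoms than exposure predicts, so P on E.
- Analysis section: PHQ-ADS against exposure, so P on E.
- Computing clause: E on P.

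Three cues point one way, and the clause that states the computation points the other.

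**The case against.** The strongest reply is that the plan, read as a whole, already fixes the direction correctly. The sentence on explained variance, the name stressor reactivity, the sign rule and the analysis section all treat symptoms as the response to exposure. The adverse scenario needs an analyst to follow one loosely worded clause, overlook the next sentence and the analysis section, and still apply the sign rule that belongs to the intended fit. On this view the point is editorial.

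Most of that stands. A reader might infer that the planned score really has the wrong sign, mainly measures exposure, and will make a beneficial programme look harmful. The documents do not support that: the positive arm differences above measure a literal misreading and rest on an assumed correlation.

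A reader might also infer that the symptom score is left open, because the measures section lists PHQ-ADS, PHQ-9 and GAD-7. That too is weak, because the analysis section names PHQ-ADS for the arm comparison, which can be read as narrowing the list.

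The reply does not remove the contradiction. The misworded clause sits in the only description of how to compute the score. Nor would the variance criterion expose a wrong-way fit: in simple linear regression R² is the same in both directions, so the same exposure score would be selected either way.

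**Conclusion.** The point holds as a minor correction to the definition of a secondary outcome. The computing clause is stated backwards and contradicts its own paragraph and the analysis section. P on E is clearly intended, and under it the sign rule is correct.

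Only if the clause were applied literally with the stated sign would a symptom benefit of d = 0.3 appear as a shift of about +0.1 to +0.2 SD towards lower resilience. That size assumes an E-P correlation of 0.3 to 0.6 and no effect on exposure. The direction needs only a positive correlation and that same absence of an effect on exposure. The primary outcome, its analysis and the sample size are untouched.

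**What to change.** In Secondary outcome measures, replace the computing clause with wording such as: *PHQ-ADS (P) is regressed on stressor exposure (E); the SR score is the observed PHQ-ADS minus the PHQ-ADS predicted from E; positive values mean less resilient.* This agrees with the analysis section and leaves the existing sign rule as it is.

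The cost is one sentence. It needs no new data and no change to the mixed model. It can be settled before any analysis, since the article plans no interim analyses and will analyse only once data collection is complete.

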#### Other measures

Sociodemographic information is collected at all timepoints. During the screening, basic information (e.g. gender, age, education), information regarding migration (e.g. time spent in the Netherlands), and work (e.g. sector, working hours, income source, contract type) are collected. At baseline, further information is collected (e.g. relationship status, living situation). Potentially fluctuating sociodemographic information is recollected at follow-up assessments.

Exposure to potentially traumatic events will be assessed using a shortened version of the Brief Trauma Questionnaire (BTQ) [71]. The BTQ comprises 10 items, each corresponding to an event that can be indicated as either having occurred or not. To accommodate follow-up, minor adaptations were made to the BTQ.

Impacts of COVID-19 will be assessed with a questionnaire based on other COVID-19 questionnaires [72]. It consists of 16 items focusing on various aspects of the COVID-19 pandemic (e.g. COVID-19 infection, adherence to and consequences of COVID-19 regulations) and an additional item on vaccination status at baseline assessment.

After the trial, various implementation indicators, e.g. reach, dose, resource use, and costs (training, staff, recruitment etc.), will be assessed. Furthermore, based on the implementation indicators and fidelity data the incremental costs per change in the primary outcome and quality of life will be estimated.

Hair cortisol concentrations (HCC), cortisone, dehydroepiandrosterone (sulphate) (DHEA(S)), testosterone, and progesterone levels will be analysed through hair samples. In about 100 hair strands, cut as close as possible from the scalp at the vertex posterior, the 3cm hair from the scalp will be analysed for cumulative HCC, cortisone, and DHEA(S) levels [39]. Based on an average hair growth rate of 1 cm/month [73], this will give an indication of physiological stress levels over 3 months. Participants will be instructed to obtain a hair sample with the assistance of another person. As support, an instruction video has been created. In addition, participants are asked to complete a hair questionnaire to assess several relevant hair-specific characteristics (e.g. on hair washing, hair treatments and on substance or medication use such as corticosteroids).

Video records of PM + sessions will be analysed for digital markers of facial activity (e.g. happiness, sadness, and fear), voice (e.g. speech prevalence), and movement (e.g. head pitch). This will be done using open-source tools based on the analysis by Galatzer-Levy et al. [74].

#### Translation and adaptation of the study measures

When available, instruments translated and/or validated in Polish were selected. In line with WHO guidelines on the translation and adaptation of research instruments [75], instruments without existing Polish translations were translated and back-translated. In case of discrepancies in translation, items were discussed by the translators to reach consensus.

## Interventions

### Psychological First Aid (PFA)

Two to five days after screening, all participants will receive Psychological First Aid (PFA) by telephone. PFA is a support strategy for someone who is experiencing psychological distress and may need support. It consists of various themes, such as assessing and addressing (basic) needs and concerns, providing practical care and support, listening and comforting people, connecting them to information and protecting them from further harm [32]. At the end of the phone call, participants will be informed of the group they have been randomized into.

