#### Assessments

After screening, data is collected through self-report assessments at four time points: *t*_1_ (baseline, week 1 – sent at the end of screening), *t*_2_ (post-DWM, week 7), *t*_3_ (post-PM + , week 13), and *t*_4_ (follow-up, week 21) with the online programme Castor Electronic Data Capture (EDC) [46]. Each digital assessment with questionnaires will be sent to participants via e-mail and can be completed through any device with Internet access (e.g. smartphone, laptop, tablet). Total completion time of each digital assessment is about 30 min (see ‘Study measures’).

Participants have 14 days to complete the questionnaire When an assessment remains incomplete, participants will receive a maximum of 3 reminders on days 2, 5, and 10 through different communication channels to promote participant retention. Hair samples and (paper) questionnaires are collected at *t*_1_ and *t*_4_ through regular mail. Once the research team receives the hair sample and the hair questionnaire, answers are entered in Castor EDC as well. Participants receive a 10-euro gift voucher for each completed assessment with a maximum of 4 vouchers (*t*_1_-*t*_4_), regardless of whether they send a hair sample.

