#### Screening measures

Psychological distress will be measured with the K10 [47]. The K10 consists of ten items that focus on anxiety and depression-related distress over the past 30 days. Items are scored on a five-point Likert scale (1–5), giving a total score of 10–50 with higher scores representing higher levels of distress. In line with previous research [48, 49] a cut-off score of > 15.9 is used, which indicates psychological distress [50]. The K10 is validated in various languages (e.g. Dutch) [51].

 Suicidal ideation will be assessed with the suicidal thoughts interview from the PM + manual (*t*_0_*,* screening) [52] or with a screening question used in a previous trial testing an e-health intervention (*t*_2_-*t*_4_) [53]. If a participant answers positively to this screening question (*t*_2_-*t*_4_), a message will appear with information on where to get help and stating that a member of the research team will reach out to the participant. Once a phone call has been scheduled with the participant, an assessor will administer the suicidality module of the Mini-International Neuropsychiatric Interview (MINI) [54]. Suicidal ideation is not assessed during *t*_1_ as this directly follows screening. Cognitive impairment will be assessed with the observation checklist from the PM + manual.

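### Baseline PHQ-ADS, the covariate in the primary model, can be completed after participants have been told their arm

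*Protocol article*

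**What the plan says.** All references are to the Protocol article.

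- *Assessments* describes t1 as "baseline, week 1 – sent at the end of screening". On the route it says: "Each digital assessment with questionnaires will be sent to participants via e-mail". On the time allowed it says: "Participants have 14 days to complete the questionnaire". No exception is made for t1. For an incomplete assessment, "participants will receive a maximum of 3 reminders on days 2, 5, and 10".
- *Psychological First Aid (PFA)* says: "Two to five days after screening, all participants will receive Psychological First Aid (PFA) by telephone". It continues: "At the end of the phone call, participants will be informed of the group they have been randomized into".
- *Randomization* gives the group sizes, the block sizes and the system. It does not say whether t1 must be complete first.
- *Study measures* makes the PHQ-ADS items mandatory for moving on within an assessment. That is not a condition for randomisation, the PFA call or disclosure.
- *Screening measures* leaves the suicidality question out of t1 "as this directly follows screening".
- *Quantitative data (RCT)*, under Data analysis, specifies for the primary model "a baseline measure of the PHQ-ADS as a covariate, and subjects as random effects". It also says that missing data are not imputed and that the intention-to-treat analysis includes all randomised participants.

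**The concern.** Adjusting for a baseline score is safe because treatment assignment cannot have influenced it. That protection is lost for anyone who answers t1 after being told the arm. PHQ-ADS is self-reported, and a participant disappointed at being in the control group, or encouraged by being offered the programme, may answer differently. The covariate then carries part of an effect of allocation, and adjusting for it moves the estimated difference at t4. The other self-report measures taken at t1 are exposed in the same way. Whether t1 is completed at all could also come to depend on the arm, and a participant without the covariate would normally drop out of the adjusted model.

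The timing statements also fit together poorly. *Screening measures* treats t1 as immediate, while *Assessments* allows it two weeks.

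**Working it through.** **1. Timeline.** Day 0 is the end of screening. Reminder days are assumed to count from dispatch of t1.

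- Day 0: t1 e-mailed.
- Day 2: first reminder; earliest PFA call and disclosure.
- Day 5: second reminder; latest PFA call and disclosure.
- Day 10: third reminder.
- Day 14: t1 closes.

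Time for which t1 stays open after disclosure = 14 − day of disclosure:

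- disclosure on day 5: 14 − 5 = 9 days, 9/14 = 64% of the window;
- disclosure on day 2: 14 − 2 = 12 days, 12/14 = 86% of the window.

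These are shares of the window, not of participants.

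**2. Who is affected.** If calls keep to schedule, anyone answering the day-10 reminder answers after disclosure. Someone answering the day-2 or day-5 reminder may do so before or after, depending on the day of the call and how quickly they respond. Someone who completes t1 at once is unaffected.

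**3. Effect on the primary contrast.** In a covariate-adjusted comparison,

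adjusted difference = (difference in outcome means) − slope × (difference in baseline means).

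If a share f answers late and disclosure shifts their reported baseline by s SD between arms, the size of the bias is about slope × f × s. The documents give none of the three values, so all are assumptions:

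- low: 0.5 × 0.10 × 0.1 = 0.005 SD;
- middle: 0.6 × 0.20 × 0.2 = 0.024 SD;
- high: 0.7 × 0.40 × 0.3 = 0.084 SD.

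Against the target d of 0.3 (*Sample size*), these are 0.005/0.3 = 2%, 0.024/0.3 = 8% and 0.084/0.3 = 28%.

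**4. Direction.** Lower PHQ-ADS is better. If, after disclosure, intervention participants report lower baselines or controls higher ones, adjustment takes away part of a real benefit and the bias is toward the null. The reverse pattern exaggerates the benefit. The documents do not say which to expect.

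**5. Recall period.** *Secondary outcome measures* says PHQ-9 and GAD-7 cover the preceding two weeks. For t1 completed on day 10, the part of that period after disclosure is 10 − 5 = 5 to 10 − 2 = 8 days of 14 (36 to 57%). On day 14 it is 9 to 12 days (64 to 86%).

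**The case against.** The strongest reply is that the order may be fixed where we cannot look. Figure 1 is the trial flowchart and Table 1 the schedule of enrolment and assessments. Neither is shown, and the full protocol or the Castor set-up may hold back allocation until t1 is in. That stands as a limit on the point but does not remove it. If disclosure did wait for a t1 that may arrive on day 14, the statement that all participants are called on days two to five and told their arm on that call could not hold as written. The text would need a correction either way.

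A second reply is that 14 days is a maximum written for assessments in general, and that *Screening measures* expects t1 straight away, so late baselines are the exception. This stands in part. It is a good reason to expect a small share, but it sets no deadline.

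A third is that the two-week recall period dilutes any reaction to disclosure. It does for a t1 completed soon after the call, less so towards day 14. Nor does it prevent knowledge of the arm from colouring how the whole period is rated.

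A reader might infer more than the documents support:

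- That everyone who answers the day-5 reminder already knows the arm. This does not follow, since the call may come later on day 5.
- That PFA itself distorts the comparison. Both arms receive it, so a baseline taken after PFA but before disclosure creates no difference between arms by that route.
- That the primary result will be materially biased. The share and the shift are unknown, and the low end of the range is negligible.

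**Conclusion.** The point holds as a conflict between stated timings. On the visible text, the covariate of the primary model can be measured after the participant knows the arm, and the reminder schedule prompts some participants to do so. How many is unknown and may be few. The bias of about 0.005 to 0.08 SD rests on assumed values for the slope, the late share and the differential shift, and its sign is open. It is worth correcting because the change is cheap and protects the primary analysis. It is not evidence that the trial's estimate is wrong.

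**What to change.** **Participants not yet enrolled.** State, and enforce in Castor, that the t1 PHQ-ADS is submitted before randomisation, or at least before the arm is disclosed. *Trial status* gave 138 enrolled at the time of writing, which left 212 − 138 = 74; the number will have fallen since.

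**Participants already enrolled.** Use the system's time stamps to report, by arm, how many t1 were completed after disclosure. Keep all randomised participants in the primary analysis. Do not set late baselines to missing: covariates are not imputed under the plan, so those participants would normally leave the adjusted model, selected on behaviour after disclosure. That would break the intention-to-treat set and could add more bias than it removes. Instead, prespecify before the data are analysed a sensitivity analysis with the screening K10 as the baseline covariate for everyone, since it is always measured before disclosure.

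**Text.** Reconcile *Assessments*, *Screening measures* and *Psychological First Aid (PFA)* on when t1 is completed relative to the call, including the premise on which the suicidality question is left out of t1.

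**Cost.** A system rule and a few sentences. Slow responders learn their arm later, and those who never complete t1 are not randomised, or not told their arm. The K10 may predict PHQ-ADS at t4 less well than baseline PHQ-ADS does, so the sensitivity analysis may be somewhat less precise.
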